#### 10.1.5 Final visit: (*Visit 11*= Week 88 +/-1.5 week) OR Early termination visit

The following procedures and evaluations are to be performed at the final visit:

- Obtain Vital Signs (orthostatic blood pressure, respiration, oxygen saturation, heart rate, temperature, weight).
- Review and document concomitant medications.
- Perform general Physical Exam: general appearance, head, eyes, ears, nose, neck, and throat, lungs, heart, peripheral pulses and skin.
- Perform a complete neurological exam: orientation to self, time and place, speech observation, cranial nerves, strength, sensory, reflexes, gait, and cerebellar.
- Assess changes in diet, physical activity and sleep patterns during the study.
- Assess Covid-19 disease during the study
- Assess MDS-UPDRS (Movement Disorders Society Unified Parkinson's disease Rating Scale). The MDS-UPDRS-III will be videotaped for rating assessment by other two-movement disorder specialists.
- Assess H&Y (Hoehn and Yahr scale).
- Assess TUG (Timed Up and Go Test).
- Administer MoCA (Montreal Cognitive Assessment).
- Provide UPSIT (University of Pennsylvania Smell identification test) for self-administration.
- Administer the Since last time version of the Columbia–Suicide Severity Rating Scale (C-SSRS).

- Provide ADL (Schwab and England Activities of daily living score) for self-administration.
- Provide EQ-5D-5L (EuroQol- 5Dimension).
- Provide GDS-SF (Geriatric Depression Scale Short form).
- Provide PAS (Parkinson Anxiety Scale).
- Provide PDQ-39 (Parkinson's Disease Questionnaire) for self-administration.
- Provide RBD-Single-Question Screen (RBD1Q).
- Urine sample for Dipstick urinalysis.
- Collect blood samples for:
  - DSA (Donor specific antibodies)- Order as HLA typing.
  - Peripheral markers: Neurotransmitters, Oxidative stress, cytokines, chemokines, and growth factors.
  - $\alpha$ -synuclein oligomers levels.
- Collect urine sample for  $\alpha$ -synuclein oligomers
- Assess the Need for change in symptomatic therapy.

## 10.2 Telephone or email evaluations

These will occur at week 1, week 4, week 13, week 19, week 23, week 31, week 38, week 44, week 55, and week 75. In order to maintain continuous monitoring of the presence of AEs after the infusion visit, patients would either receive a phone call or an email to monitor signs or symptoms of adverse reactions to the transfusion, at regular intervals until the study end, with a total of 10 evaluation calls/emails (*See appendix O for a copy of the Telephone evaluation form*).

### 10.3 Study Timeline

[figure not shown]

### 10.3 Study Schedule

|                     |                                                                  |                           |                            | Treatment Period |                           |                          |                            |                          | Follow up Period              |                               |                            |                               |                            |                                   |
|---------------------|------------------------------------------------------------------|---------------------------|----------------------------|------------------|---------------------------|--------------------------|----------------------------|--------------------------|-------------------------------|-------------------------------|----------------------------|-------------------------------|----------------------------|-----------------------------------|
|                     |                                                                  | Screen visit              | BL                         | INF 1            | Safety/
Clinical       | INF 2                    | Safety/
Clinical        | INF 3                    | Safety/
Clinica
1       | Safety/
Clinica
1       | Safety/
Clinical        | Final
visit                | Un-
schedule
d visit | Early
termina
tion
visit |
|                     | VISIT #                                                          | 1                         | 2                          | 3                | 4                         | 5                        | 6                          | 7                        | 8                             | 9                             | 10                         | 11                            |                            |                                   |
|                     | WEEKS                                                            | Week
-12 to
week -3 | Week -
11 to
week -1 | 0                | Week 9
+/-
1.5 week | Week 18
+/-
1 week | Week 27
+/-
1.5 week | Week 36
+/-
1 week | Week 40
+/-
1.5
week | Week 49
+/-
1.5
week | Week 62
+/-
1.5 week | Week 88
+/-
1.5
week |                            |                                   |
| Clinical Assessment | Demographics, EKG, Specialty
labs*                            | X                         |                            |                  |                           |                          |                            |                          |                               |                               |                            |                               |                            |                                   |
|                     | Physical and neurological
examination. Meds review            | X                         |                            | X                | X                         | X                        | X                          | X                        | X                             | X                             | X                          | X                             | X                          | X                                 |
|                     | Vital Signs                                                      | X                         | X                          | X                | X                         | X                        | X                          | X                        | X                             | X                             | X                          | X                             | X                          | X                                 |
|                     | UPSIT & MOCA                                                     | X                         |                            |                  |                           |                          |                            |                          |                               | X                             |                            | X                             |                            | X                                 |
|                     | MDS- UPDRS, TUG, H&Y (OFF)                                       | X                         |                            |                  | X                         |                          | X                          |                          | X                             |                               | X                          | X                             |                            | X                                 |
|                     | MDS-UPDRS On                                                     | X                         |                            |                  |                           |                          |                            |                          |                               |                               |                            |                               |                            |                                   |
|                     | Questionnaires: ADL, PAS, GDS, PDQ-
39, C-SSRS, EQ-5D-5L, NMS | X                         |                            |                  | X                         |                          | X                          |                          | X                             |                               | X                          | X                             |                            | X                                 |
| Laboratory          | Lumbar puncture**                                                |                           | X                          |                  |                           |                          |                            |                          |                               | X                             |                            |                               |                            |                                   |
|                     | CBC with differential and CMP                                    | X                         |                            |                  | X                         |                          | X                          |                          | X                             |                               |                            | X                             |                            | X                                 |
|                     | Dipstick UA                                                      | X                         |                            |                  |                           |                          |                            |                          |                               |                               |                            | X                             |                            |                                   |
|                     | Blood*** for peripheral markers                                  |                           | X                          |                  | X                         |                          | X                          |                          | X                             | X                             |                            | X                             |                            | X                                 |
|                     | Plasma $\alpha$ -synuclein oligomers                             |                           | X                          |                  |                           |                          |                            |                          | X                             | X                             |                            | X                             |                            | X                                 |
|                     | Donor Specific Antibodies                                        |                           | X                          |                  | X                         |                          | X                          |                          | X                             |                               |                            | X                             |                            | X                                 |
|                     | Infusion procedure and 4 hours
Observation                    |                           |                            | X                |                           | X                        |                            | X                        |                               |                               |                            |                               |                            |                                   |
|                     | Neuroimaging                                                     |                           | X                          |                  |                           |                          |                            |                          | X                             |                               |                            | X                             |                            | X                                 |

\*Specialty labs include INR, PT, and PTT.

\*\*CSF for CBC + diff, glucose, protein, Neurotransmitters, Oxidative Stress Markers,  $\alpha$ -synuclein oligomers, Cytokines, Chemokines, and Growth Factors.

\*\*\* Serum for Neurotransmitters, Oxidative Stress Markers, Cytokines, Chemokines, and Growth Factors.

## 11. Potential adverse events

### 11.1 Infusion-Related Allergic Reactions

The investigators will ensure that appropriate best clinical practices and treatment are initiated should an event indicating an allergic or hypersensitive reaction occur. Each event will be recorded as an AE or SAE, depending on which criteria are met by the event. The start and stop/restart times must be recorded in the CRF.

Should an infusion-related allergic reaction occur the infusion will be stopped immediately, and the subject closely monitored until stable. An infusion-related allergic reaction may appear as flushing, sudden rash, or shortness of breath or difficulty breathing.

Definitions and grading will follow the current NCI-CTCAE criteria. The current definitions and suggested treatment plans for an infusion-related allergic reaction are listed below:

#### **Grade 1:**

Mild transient reaction

1. Stop infusion and evaluate for severity. If reaction remains a grade 1, then restart at a reduced rate.
2. Reduce infusion rate by 50%,
3. Treat subject per good clinical practice (suggest antihistamines, corticosteroids, etc. as medically indicated) and monitor for worsening condition.
4. If the reaction persists or worsens, the infusion will be discontinued.

#### **Grade 2:**

Readily responds to clinical treatment (e.g., antihistamines, corticosteroids); should consider prophylactic treatment for  $\leq 24$  hours.

1. Pause infusion for up to 2 hours (product should not be infused after 4 hours).
2. Administer clinical treatment for the allergic reaction as medically indicated.
3. Resume infusion at 50% of the previous rate once the reaction has decreased to Grade 1 in severity. Monitor closely for any worsening.
4. If the reaction reoccurs, stop the infusion. Study treatment is to be discontinued.

#### **Grade 3:**

Prolonged or severe reaction (e.g., not rapidly responsive to treatment or a recurrence of reaction after an initial improvement of a Grade 1 or Grade 2 reaction).

1. Discontinue infusion immediately. Study treatment is to be discontinued
2. Administer clinical treatment for the allergic reaction as medically indicated.
3. Report as an SAE

#### **Grade 4:**

Characterized as life-threatening AE; urgent intervention indicated to maintain hemostasis.

1. Discontinue infusion immediately. Study treatment will be discontinued.
2. Administer clinical treatment for the allergic reaction as medically indicated.
3. Report as an SAE

#### **11.1.2 Algorithm for response in case of an allergic reaction.**

[figure not shown]

## 11.2 Sensitization to Donor Specific Antibodies (DSA).

There is a possibility of anti-donor alloimmune response after the first or second infusion of MSC, which might lead to a subsequent antibody-mediated rejection (AMR) with the following infusion. IF DSA are identified at either week 8 or 21 patients would be put on hold of their regular schedule on infusions and the PI will follow the algorithm describes in 11.2.1.

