## 10. Study schedule

The study will last a total of one year and 8 months (88 weeks) per patient (3 groups) and will include 11 clinical visits and 10 telephone evaluations (*Please see section 10.3 for the study timeline and 10.4 for study schedule*).

There are 6 types of clinical visits: Screening, Baseline, Infusion, Safety and Clinical assessment, unscheduled visit, and final visit plus phone call evaluations starting after the first infusion.

- Visit #1 Screening Visit (between week -12 to week -3): after signing the consent and discussing the purpose and timeline of the study, the PI will confirm the PD diagnosis and establish the current disease stage. At this visit, the CRU staff will collect blood for laboratory assessment. The purpose of this visit is to ensure that the patient meets the inclusion and exclusion criteria.
- Visit #2 Baseline visit (between week -11 to week-1): the purpose of this visit to obtain baseline measurements on serum, plasma, CSF, and neuroimaging.
- Visit #3 Infusion Day (week 0): First IV MSCs infusion.
- Visit #4 Clinical and Safety assessment (week 9+/-1.5 week): the purpose of this visit is to determine the safety and the immediate immunological, physical and neurological response to the first infusion.
- Visit #5 Infusion Day (week 18+/-1 week): Second IV MSCs infusion.
- Visit #6 Clinical and Safety assessment (week 27+/-1.5 week): the purpose of this visit is to monitor safety and the immunological, physical and neurological response to the second infusion.
- Visit #7 Infusion Day (week 36+/-1 week): Third IV MSC infusion
- Visit #8 Clinical and Safety assessment (week 40+/-1.5 week): the purpose of this visit is to monitor the safety and the immunological, physical and neurological response to the third infusion. Additionally, to collect enough data for our first interim analysis.

- Visit #9 Clinical and Safety assessment (week 49+/-1.5 week): the purpose of this visit is to monitor the safety and the immunological, physical, and neurological response to the infusions.
- Visit #10: Clinical and Safety assessment (week 62+/-1.5 week): the purpose of this visit is to monitor the safety and the immunological, physical, and neurological response to the infusions.
- Visit # 11: Final visit (week 88+/-1.5 week): the purpose of this visit is to determine the physical and neurological response to the complete MSC treatment.

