- Provide PDQ-39 (Parkinson's Disease Questionnaire) for self-administration. (All visits except visit 9)
- Collect blood samples for:
  - DSA (Donor specific antibodies). Order as HLA typing. (**All visits except visit 9 & 10**)

- Peripheral markers: Neurotransmitters, Oxidative stress, cytokines, chemokines, and growth factors. (*All visits except visit 10*)
- $\alpha$ -synuclein oligomers levels. (*Only at visit 8 & 9*)
- Performed Neuroimaging in the levodopa OFF state (*Only at visit 8*):
  - High-resolution T1- & T2-weighted MRI.
  - Perfusion MR.
  - Diffusion-weighted MRI.
  - Neuromelanin MRI.
- Performed Lumbar Puncture and observe for 2 hours (*Only at visit 9*)
- Collect urine sample for  $\alpha$ -synuclein oligomers (*Only at visit 9*)
- CSF samples for:
  - CBC with differential.
  - Glucose and Protein levels
  - $\alpha$ -synuclein oligomers
  - Markers: Neurotransmitters, Oxidative stress, cytokines, chemokines, and growth factors.
- Review DSA results from the previous visit. (*Only at visit 4 & 6*):
- Assess the Need for change in symptomatic therapy.

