|                 |                                                    |                                              |                                                                          |                                                                     |                           |                           |                          |                             |                                                |
|                 |                                                    |                                              |                                                                          |                                                                     |                           |                           |                          |                             |                                                |
|                 |                                                    |                                              |                                                                          |                                                                     |                           |                           |                          |                             |                                                |
|                 |                                                    |                                              |                                                                          |                                                                     |                           |                           |                          |                             |                                                |
|                 |                                                    |                                              |                                                                          |                                                                     |                           |                           |                          |                             |                                                |

\*Visit #: 1 = Scr, 2 =BL, 3 = inf # 1, 4 = wk 7, 5 = inf# 2, 6 = wk 20, 7 = inf# 3, 8 = wk 29, 9 = wk 39, 10 = wk 52, 11 = wk 78, or phone visit = Pv date

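### The antibody hold rule in 11.2 cites week 21, when no sample is taken, and omits the week-27 draw, the only one between infusions 2 and 3

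*Protocol*

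**What the plan says.** Section 11.2 warns that a patient may become sensitised after the first or second infusion and may then reject the cells at the following one. It sets the rule: "IF DSA are identified at either week 8 or 21 patients would be put on hold of their regular schedule on infusions". The investigator is then to follow the algorithm in 11.2.1, a figure that is not visible in the public document.

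Section 10 places infusions 1, 2 and 3 at weeks 0, 18 and 36. The safety visit after infusion 1 is visit 4, at week 9 ± 1.5. The one after infusion 2 is given as "Visit #6 Clinical and Safety assessment (week 27+/-1.5 week").

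In 10.1.4, DSA is drawn at "All visits except visit 9 & 10", that is, at visits 4, 6 and 8. The schedule table, in the row "Donor Specific Antibodies", agrees and adds baseline, the final visit (week 88) and early termination. Section 10.1.4 also lists, at visits 4 and 6 only, the step "Review DSA results from the previous visit".

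Section 8.6 requires DSA testing between infusions and at 6 and 12 months after the last one. It says that sensitised patients move to a modified infusion schedule. It names no weeks and points to 11.2.1.

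**The concern.** The hold rule is a patient-level safety rule for a repeat-dose allogeneic cell product. It has to connect a scheduled blood sample to the decision on the next infusion. For infusion 2 it does so, if loosely: week 8 lies inside the visit 4 window. For infusion 3 it points to a week with no sample and leaves out the sample that could trigger it.

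Read literally, the only draw the rule covers is taken before infusion 2. That sample cannot show sensitisation caused by infusion 2, although 11.2 names the second infusion as one of the two events of concern. A patient who turns positive at week 27 meets no condition in 11.2 for holding the week-36 dose.

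**Working it through.** No sample-size or error-rate calculation applies. The check compares the two weeks in 11.2 with every window in the schedule.

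**Windows (nominal week ± tolerance, section 10)**

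| Event | Window (weeks) | DSA draw |
|---|---|---|
| Visit 4 | 9 ± 1.5 = 7.5 to 10.5 | yes |
| Visit 5, infusion 2 | 18 ± 1 = 17 to 19 | no |
| Visit 6 | 27 ± 1.5 = 25.5 to 28.5 | yes |
| Visit 7, infusion 3 | 36 ± 1 = 35 to 37 | no |
| Visit 8 | 40 ± 1.5 = 38.5 to 41.5 | yes |

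Telephone contacts (10.2) include "week 13, week 19, week 23, week 31", each ± 7 days. Those nearest to week 21 cover weeks 18 to 20 and 22 to 24. They involve no blood draw.

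**Matching the rule**

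- Week 8 lies in 7.5 to 10.5, so it fits visit 4.
- Week 21 lies in no clinic window and no telephone window. It is 25.5 − 21 = 4.5 weeks before visit 6 opens.
- The only DSA draw between infusions 2 and 3 is visit 6.
- Taking the rule's week as the date a result comes back does not help. At week 21 the latest sample in hand is from visit 4, taken before infusion 2.

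**Interval from draw to infusion 3**

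- Visit 4 draw: 35 − 10.5 = 24.5 to 37 − 7.5 = 29.5 weeks before.
- Visit 6 draw: 35 − 28.5 = 6.5 to 37 − 25.5 = 11.5 weeks before.

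The sample left out is therefore the relevant one, and there is time to act on it.

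**Other steps that might close the gap**

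- The review listed in 10.1.4 at visit 6 concerns the previous visit. Visit 5 has no DSA draw, so the wording does not clearly cover the visit 6 sample.
- The infusion-visit checklist in 10.1.3 contains no DSA check.
- The DSMB (section 16) reviews aggregate data one month after each infusion. After infusion 2 that is about weeks 21 to 23, before the visit 6 sample exists.

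**How many patients the rule guards at infusion 3**, with 15 per arm. The order of doses in the two-dose arm is not stated in the visible text.

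| Two-dose arm order | MSC at infusion 3 after earlier MSC | Of these, with MSC at infusion 2 (visit 6 is the only draw after it) |
|---|---|---|
| MSC, MSC, placebo | 15 + 0 = 15 | 15 |
| MSC, placebo, MSC | 15 + 15 = 30 | 15 (visit 4 already follows the two-dose arm's only earlier MSC dose) |
| placebo, MSC, MSC | 15 + 15 = 30 | 30 |

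**Likely origin (an inference)**

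The Appendix E footnote gives visits as "4 = wk 7, 5 = inf# 2, 6 = wk 20, 7 = inf# 3, 8 = wk 29" and "9 = wk 39, 10 = wk 52, 11 = wk 78". If the same ± 1.5 weeks applied, visit 4 would be 5.5 to 8.5, which contains 8, and visit 6 would be 18.5 to 21.5, which contains 21. Weeks 29, 39, 52 and 78 also remain in 5.1.2, week 29 in 14.4 and week 78 in 13.1. Appendix O implies infusion 3 at about week 26. The weeks in 11.2 look like remnants of a shorter calendar.

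**A separate small mismatch**

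Six months after the last infusion is 36 + 26 = week 62, which is visit 10. Section 8.6 promises a draw then, but 10.1.4 and the schedule table have none.

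**The case against.** The strongest reply is that the intent is plain despite the wrong number. Section 11.2 itself speaks of a response after the first or second infusion. Section 10 gives visit 6 the purpose of monitoring the immunological response to the second infusion, and 8.6 puts sensitised patients on a modified schedule without naming a week. There is one site, the investigator applies the algorithm, and only one draw lies between infusions 2 and 3. Nobody is told to ignore a positive week-27 result. The 11.2.1 figure and the study timeline are not visible and may show the right visits.

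The consequence may also be small. Phase I saw no response to donor HLA. Section 3.5 reports no life-threatening host-versus-graft responses despite alloantibodies after repeated doses, and section 3.4 cites serial-infusion studies without specific reactions. Four-hour monitoring, the infusion-reaction rules and DSMB review give further protection.

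Much of this stands. The intent can be recovered, no number of affected patients can be derived, and the unseen figures cannot be judged. But Phase I gave single infusions only, so it says little about sensitisation on repeat dosing. Monitoring during and after an infusion does not replace a decision not to give it. The general statement in 8.6 sends the reader to the part of the protocol where the weeks are wrong. The visible text of the specific rule remains incorrect.

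**Conclusion.** The rule is wrong as written and should be fixed. Week 21 corresponds to no sample, and the week-27 draw, the only one that can show sensitisation from infusion 2 before infusion 3, is not named. This follows directly from the schedule and needs no outside assumption.

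The patients whose third infusion depends on that draw number 15 (the three-dose arm) under any dose order, rising to 30 if the two-dose arm receives placebo first. The rule as a whole guards 15 or 30 re-exposures at infusion 3, depending on that order. All these counts assume full enrolment of 45 and are ceilings. The practical risk is reduced by 8.6 and possibly by the unseen 11.2.1 algorithm. The explanation by an older calendar is an inference, and the main point does not rest on it. The missing week-62 draw is minor and affects data collection only.

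**What to change.** - **Section 11.2:** replace the two weeks with the DSA draws at visit 4 (week 9 ± 1.5) and visit 6 (week 27 ± 1.5). Check the 11.2.1 figure for the same outdated weeks.
- **Sections 10.1.4 and 10.1.3:** state that the visit 4 result must be reviewed before infusion 2 (visit 5) and the visit 6 result before infusion 3 (visit 7). The interval is 6.5 to 11.5 weeks in both cases (for visit 4 to infusion 2: 17 − 10.5 = 6.5 and 19 − 7.5 = 11.5). Add the check to the infusion-visit list.
- **Section 8.6 (minor):** either delete the 6-month draw or add DSA at visit 10.

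The first two changes are wording only, with no new visit, sample or analysis. Keeping the 6-month draw costs one extra DSA sample per patient.
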